## **7. OBJECTIVES**

### **7a. Primary objective and hypothesis**

Post-exertional malaise (PEM) symptoms of post-COVID-19 subjects and age/sex matched controls in response to three different exercise trials. The primary outcome is the comparison of the change in fatigue rating using the visual analog scale (VAS) 0-10 before and 48h after each training trial between the post-COVID-19 group and the control group. We hypothesize that the post-COVID-19 group will suffer from persistent fatigue at 48h after exercise compared to baseline, whereas control group will return to the baseline level at this time point.

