### **14. SAMPLE SIZE**

Determining an appropriate sample size for this study was challenging as the post-COVID-19 syndrome was new and there was no established data on the expected effect size of the interventions and the consistency of patient responses. Nevertheless, based on clinical observations from previous studies, we expected a markedly different response to exercise in patients compared to controls. Indeed, symptom variability after acute exercise in myalgic encephalomyelitis/chronic fatigue syndrome (ME/CFS) shows moderate to large effect sizes for most symptoms assessed with VAS scales. Our a priori estimate (using G\*Power) was that we would need at least 28 patients and 28 controls to detect a moderate effect size (Critical F 0.25) between groups in a within-between interaction design with a power of 80% and an alpha of 5%.

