## **20. STATISTICAL METHODS**

Analyses will be performed using IBM SPSS Statistics for Windows, version 29.0 (Armonk, NY: IBM Corp). To assess the primary outcome (post-exertional symptom exacerbation from baseline to 48h after each exercise), a mix-linear model was initially planned to analyse the differences in symptom changes following three exercise sessions (HIIT, MICT, ST), between the two groups (post-COVID-19 patients vs. control). Subject ID and the order of exercise sessions will be used as random effect in the mix-linear model. Pairwise comparisons will be performed when significant main or interaction effects are detected, using Bonferroni correction.

However, during data analysis, the aforementioned statistical plan was amended given the nature of the data (not normally distributed data). Particularly, a significant number of the control subjects responded “zero” change in the visual analog scale assessing the symptom exacerbation. As such, non-parametric tests (Mann-Whitney test, Kruskal-Wallis test) were used to compare differences in symptoms following exercise trials between the groups.

A mixed-linear model was used to analyze differences in continuous data (CPET variables, interleukin (IL)-6, Creatine Kinase) following three exercise sessions (HIIT, MICT, ST) between the two groups (post-COVID-19 patients vs. control). Subject ID and order of exercise sessions were used as random effect in the mix-linear model. Pairwise comparisons will be performed when significant main or interaction effects are detected, using Bonferroni correction.

For the physiological characterization assessments, two-tailed Chi-square test or Student t-test will be used to examine differences in categorical or continuous variables, respectively, between the post-COVID-19 patients and the control group.

Results will be presented as mean (SD), and significance will be set at  $P < 0.05$ .

Missing data will be treated as missing values in the statistical models, unless otherwise specified. In retrospect, there was no need for missing data imputation. Therefore, missing data were treated as missing values.

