| Numbers analyzed                                             | 16       | For each group, number of participants (denominator) included in each analysis and whether the analysis was by original assigned groups                                                     | Figure1              |
| Outcomes and estimation                                      | 17a      | For each primary and secondary outcome, results for each group, and the estimated effect size and its precision (such as 95% confidence interval)                                           | 18-22                |
|                                                              | 17b      | For binary outcomes, presentation of both absolute and relative effect sizes is recommended                                                                                                 | 18-20                |
| Ancillary analyses                                           | 18       | Results of any other analyses performed, including subgroup analyses and adjusted analyses, distinguishing prespecified from exploratory                                                    | 7                    |
| Harms                                                        | 19       | All important harms or unintended effects in each group (for specific guidance see CONSORT for harms)                                                                                       | NA                   |
| Comment Limitations                                          | 20       | Trial limitations, addressing sources of potential bias, imprecision, and, if relevant, multiplicity of analyses                                                                            | 9-11                 |
| Generalizability                                             | 21       | Generalizability (external validity, applicability) of the trial findings                                                                                                                   | 9-11                 |
| Interpretation                                               | 22       | Interpretation consistent with results, balancing benefits and harms, and considering other relevant evidence                                                                               | 9-11                 |

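### Section 20 tests the VAS changes by ranks but still summarises them as mean (SD), and names no group effect measure or confidence interval to go with the test

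*Combined protocol and SAP*

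**What the plan says.** Section 7a defines the primary comparison: "The primary outcome is the comparison of the change in fatigue rating using the visual analog scale (VAS) 0-10 before and 48h after each" exercise session, patients against controls. It names no between-group summary of that comparison.

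Section 20 gives the analysis in two stages. At first, "a mix-linear model was initially planned to analyse the differences in symptom changes following three exercise sessions" between the two groups. During data analysis this was dropped because the data were not normal and "a significant number of the control subjects responded" zero change. In its place, "non-parametric tests (Mann-Whitney test, Kruskal-Wallis test) were used to compare differences in symptoms following exercise trials between the groups". Section 25 dates the revision to August 2023.

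One reporting rule then covers every outcome in Section 20, with no exception for VAS: "Results will be presented as mean (SD), and significance will be set at" P < 0.05. Medians, group differences, shifts, probability measures and intervals are not mentioned. A confidence interval appears only in the appended CONSORT checklist, where item 17a asks for "results for each group, and the estimated effect size and its precision (such as 95% confidence interval" and points to pages 18-22 of an article that is not part of these documents.

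**The concern.** The test was changed and the summary was not. The mixed model would have estimated a mean difference with an interval, and mean (SD) would have described the same quantity. The Mann-Whitney test asks whether a patient's change tends to be larger than a control's. Neither group's mean answers that, and the reason given for leaving a model of means (skew and many zeros) also makes mean (SD) a poor description of these changes.

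What is at stake is how the primary result is read. There are three sessions, so three primary group comparisons. Under the plan as written, each yields a P value for one quantity beside a table of another. A reader would take the size of the effect from numbers that the P value does not test, and could not tell a session with no difference from one measured imprecisely.

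**Working it through.** **1. The plan's own figure.** The only statistical figure nearby is the sample size in Section 14: "we would need at least 28 patients and 28 controls to detect a moderate effect size (Critical F 0.25) between groups". The stated targets are 80% power at a 5% alpha. For a within-between interaction, the noncentrality is f² × N × m / (1 − ρ), with N the total, m the number of measurements and ρ their correlation. Section 14 gives neither m nor ρ.
- With m = 3 and ρ = 0, N = 56 gives 0.0625 × 56 × 3 = 10.5 and power 0.82.
- With m = 3 and ρ = 0.5, N = 28 in total gives the same 10.5 and power 0.81.

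The figure can be neither confirmed nor called wrong, and this point does not depend on it.

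**2. The measure that matches the test.** Mann-Whitney compares the groups through the probability index θ = P(patient change > control change) + ½ P(tie), with θ = 0.5 when neither group tends higher. The documents give no VAS data and no share of zeros, so the examples below are assumed data with 30 per group.

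**3. An example in line with the hypothesis.** Patients: 18 at +2, 12 at 0. Controls: 24 at 0, 3 at +1, 3 at −1.
- P(exceeds) = 0.6 + 0.4 × 0.1 = 0.64.
- P(tie) = 0.4 × 0.8 = 0.32.
- θ = 0.64 + 0.16 = 0.80, bootstrap 95% CI 0.71 to 0.89.
- Mean (SD) is 1.20 (1.00) against 0.00 (0.45).

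Mean and ranks agree in direction here. The example also shows that ties must be part of the definition: 0.64 and 0.80 are different statements about the same data.

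**4. An example where the mean misses what the test finds.** Patients: 18 at +1, 12 at 0. Controls: 3 at +6, 27 at 0.
- Mean (SD) is 0.60 (0.50) against 0.60 (1.83), a difference of 0.00 (Welch 95% CI −0.70 to 0.70).
- θ = 0.6 × 0.9 + ½ × 0.4 × 0.9 = 0.54 + 0.18 = 0.72, bootstrap 95% CI 0.60 to 0.82.
- Mann-Whitney P = 0.0005.

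The prescribed table would show identical means beside a very small P value.

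**5. The precision that goes unreported.** By the Hanley-McNeil formula, SE² = [θ(1 − θ) + (n − 1)(A − θ²) + (n − 1)(B − θ²)] / n², with A = θ/(2 − θ), B = 2θ²/(1 + θ) and n per group. For θ = 0.60 and n = 30: A = 0.4286, B = 0.4500, SE² = [0.24 + 29 × 0.0686 + 29 × 0.0900] / 900 = 0.00538, SE = 0.0733, half-width 1.96 × 0.0733 = 0.144.

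| n per group | θ = 0.47 | θ = 0.60 | θ = 0.70 |
|---|---|---|---|
| 30 (Section 9) | 0.147 | 0.144 | 0.133 |
| 40 (Synopsis) | 0.127 | 0.124 | 0.115 |

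An observed θ of 0.60 at 30 per group would run from about 0.46 to 0.74, compatible with no difference and with a large one. The formula is not built for heavy ties, so these are guide values. In the step 3 example the bootstrap half-width is 0.09, where the formula gives 0.11.

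**The case against.** **Mean (SD) is only descriptive, and the sentence does not forbid anything else.** This is partly right. The sentence closes a section that also covers mixed models and t-tests, and for those outcomes mean (SD) is an ordinary summary. A mean change on a 0-10 scale is also readable. But for the rank-tested outcomes no other summary is planned. A reader who rebuilds an interval from means, SDs and group sizes gets one for the mean difference, which in step 4 is centred on zero while the test rejects.

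**Checklist item 17a claims effect sizes and intervals.** The article pages it cites cannot be checked here, so nothing can be said about what was finally reported. The item is standard checklist wording and selects no measure. The gap is shown for the plan, not for the publication.

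**A stronger reading is tempting: that the means and the P value will point in opposite directions.** Such data can be built. With 30 per group, put 20% of patients at +7, 60% at −1 and 20% at 0, against controls with 90% at 0 and 10% at +1. The mean difference is then +0.70 while θ = 0.29 with P = 0.002. This needs a small group with large changes set against small opposite changes or zeros in the rest. In six simulated zero-heavy scenarios (4,000 trials each; controls 60-70% forced zeros, patients 20-30%), the signs differed in 0 to 11% of trials, and in none when P < 0.05. Section 10 requires patients to report worsening after exertion, and Section 7a expects persistent fatigue in patients and recovery in controls. Under that pattern both summaries would normally agree in direction. The documents do not support reversal as an expected result.

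**Conclusion.** The point holds as a mismatch between test and summary for the VAS outcomes. Section 20 names no effect measure or interval for the primary comparison, and mean (SD) does not stand in for one. At the two sample sizes in the documents, the missing interval is about plus or minus 0.13 to 0.15 on θ at 30 per group and 0.11 to 0.13 at 40, for θ between 0.47 and 0.70. This rests on the Hanley-McNeil approximation; the true widths depend on the share of ties, which the documents do not give.

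It should be changed, because it governs how the primary answer is read. It does not make the rank test invalid, does not fault mean (SD) for the mixed-model and t-test outcomes, and does not show that any result was misreported or reversed.

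**What to change.** Replace the reporting sentence in Section 20 with a rule by type of outcome.
- **Rank-tested VAS outcomes**, by group and session: median (IQR); the shares with decreased, zero and increased change; and θ, defined with ties counted as half, with a 95% CI from a tie-appropriate method such as the bootstrap. Mean (SD) may stay as a supplement.
- **Mixed-model outcomes** (CPET variables, IL-6, creatine kinase): mean (SD) as description, plus model-based differences with 95% CIs.
- **Characterization outcomes under t-tests:** mean (SD) stays as the descriptive summary.

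θ is preferable to the Hodges-Lehmann shift, which moves in steps under heavy ties. In a constructed example (60% of patients at +1 and the rest at 0; five controls at +7 and the rest at 0), the shift is 0, 0.5 and 1 at 28, 30 and 40 per group, while θ is 0.66, 0.67 and 0.70.

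State that the measure was chosen after the August 2023 revision, so that it is not taken as prespecified. The cost is a few lines of text and of analysis code, with no new data.

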## **21. DATA MONITORING**

Data will be saved protected on the Department of Laboratory Medicine's server for storing research data (Redcap and Electronic lab notebook; ELN). Only responsible researchers have access to data and code key. The code key is kept with the responsible researcher. All essential data processing procedures are documented completely, clearly, and verifiably at all times. Only the study team has access to the electronic data.

## **22. HARM (BENEFIT RISK CONSIDERATION)**

The degree of exertion when measuring  $VO_{2peak}$  can give a certain feeling of discomfort in the chest and/or in working muscles. Dizziness may possibly occur with this test, but it is uncommon. Careful screening ensures that we do not include

people who are at increased risk of serious exercise related adverse events (for example, current or previous cardiovascular disease). All tests will be performed in a hospital setting, with immediate access to an emergency department. Symptoms and side effects are reported immediately to the responsible researcher and responsible physician. Specifically, in case of adverse events during the study visits, the research assistant and/or clinical staff will inform immediately the PI and responsible physician. The responsible physician will decide the appropriate sequel to solve the incidence. All details of the adverse event will be added to the medical records of the patient. PI is responsible for keeping records of the adverse event(s), including the steps taken by the research team. The strength tests performed may cause some discomfort in the leg muscles (muscle fatigue). However, these tests are associated with minimal medical risks. Exercise soreness can occur up to 4–5 days after the tests are performed. The risk of muscle, bone, joint and/or other soft tissue damage during controlled exercise is considered minimal. Needle EMG is a minimally invasive procedure that is carried out according to the clinical routines. All physiological tests are performed in a hospital environment and according to strict procedures. Muscle biopsies can in rare cases cause temporary loss of sensation. Specific care instructions are given to the research subjects. The machines are cleaned and disinfected after each use. Aggravation of symptoms and a feeling of malaise can be expected in some patients after exercise, and therefore it is important that they have contact details for the responsible physician and responsible researchers.

In regards to the direct benefits, the research subjects learn more about their current physiological function, their work capacity and their strength. The researchers also gain knowledge about what type of training is best tolerated for the individual. The potential clinical significance of this project is high, and we believe that the benefits substantially outweigh the risks of the project. Patients will be informed that their participation is voluntary, and that withdrawal will have no negative consequences for their usual treatment. There is great potential for benefit to the individual who learns more about their condition, exercise tolerance and current physiological function. Financial compensation of 1000 SEK will be given to participants for the discomfort that may possibly occur during muscle and blood sampling. It is paid after the research subject's last visit in the study.

All processions will be taken to minimize the risks as far as possible. For the tests that will be carried out, there are established test protocols that have been used for several years in our laboratory. Most examinations are routine clinical examinations performed in a hospital environment by trained personnel. Only people considered healthy enough to participate are included (see inclusion/exclusion criteria). Participants receive a direct number to the medical responsible physician ([name]) and the responsible researcher for any questions or symptoms that arise during the tests or at home after exertion. After each training session, the patients remain in our laboratory for monitoring and blood samples. They also return to the lab for follow-up 48 hours after exercise. We therefore have continuous contact with the subjects, and they also have a direct number where they can reach us at any time from home. Muscle biopsies and needle biopsy for EMG are performed according to standard procedures. We have over 10 years of experience with these samplings without complications. The research project takes place in a

hospital environment (Karolinska University Hospital in Huddinge). In the event of unexpected side findings or complications, this is noted in the patient record and the responsible physician can prescribe appropriate referrals for further examination or call emergency personnel.

## **23.AUDITING**

Study does not require external auditing. However, auditing within the research team (internally) will be conducted. Principal investigator and project manager is responsible for performing frequent auditing (monthly basis) in all data storages (see data management), ensuring that all raw material is in place for each subject.

## **24.RESEARCH ETHICS APPROVAL**

This study has been approved by the Swedish Ethical Authority REF: 2021 05758-01 and 2022-02999-02.

## **25.PROTOCOL AMENDMENTS**

Amendments have been approved by the Swedish Ethical Authority REF: 2022-02999-02. This study is registered in [ClinicalTrials.gov](https://clinicaltrials.gov/ct2/show/study/NCT05445830) NCT05445830.

The study has registered and begun following the ethical approval of the version 1.1 amendments.

The statistical plan was revised during the data analysis (Aug 2023), given that the primary outcome (post-exercise symptom exacerbation via visual analog scale) required a different statistical approach (see above).

## **26. CONSENT**

Patients attending the outpatient post-COVID-19 clinic at Karolinska University Hospital Huddinge will be informed of the current study and the opportunity to participate. Control subjects as well as post-COVID-19 patients if needed will receive information about this study through social channels and/or word of mouth. Interested patients will be in contact with the research team for further information. They will get written information via e-mail or letter. After that, the patient is given the opportunity to think and ask questions. If the person is still interested in participating, a first meeting is booked. The person then receives oral information from the responsible researcher and a chance to ask more questions if needed. The person is informed that they are free to cancel the study at any time without

having to give reasons. If the person still wants to participate, this consent is documented in writing. The screening procedure then follows.

## **27. CONFIDENTIALITY**

The requirements of the Data Protection Law are fulfilled. It is ensured that all research materials and data are adequately pseudonymized in accordance with data protection regulations prior to scientific utilization. All data is saved electronically via RedCap. All data that is collected is saved with the study ID of the research subjects as a label (sequential number). Names and personal details are not disclosed. Only involved researchers have access to data material. The code list to identify the research subjects is saved as a password-protected document with a paper copy saved in a study folder locked with the responsible researcher. The responsible researcher is responsible for all documents being archived in accordance with KI's rules for research documentation and archiving of research data (saved for at least 10 years).

## **28. DECLARATION OF INTERESTS**

No financial or other competing interests related to this study are declared by principal investigators and/or any member of the research team.

## **29. ACCESS TO THE DATA**

Access to the data will be limited to the research team or anyone involved in the data analysis. Importantly, data will be pseudonymized, and none except the research team will have access to the personal data on the subjects. Therefore, Individual research subjects cannot be identified. Data will be stored in accordance with the Karolinska Institutet guidelines for clinical research data.

## **30. ANCILLARY AND POST-TRIAL CARE**

All assessments will be conducted in the hospital setting and medical personnel will be available at any time needed. All visits/assessments will be logged in the TakeCare (medical record system). In the event of unexpected side findings or complications, this is noted in the patient record and the responsible physician can prescribe appropriate referrals for further examination or call emergency personnel. Patient insurance is in place.

## **31. DISSIMINATION POLICY**

The results will be compiled in scientific articles that will be sent to a peer-reviewed scientific journals (Open access) for assessment and possible publication as soon as the data collection and analysis work has been completed. The results can also

be communicated before publication via channels in the Stockholm region if there is a large patient benefit in the short term. Results are presented only at the group level or with fully de-identified data points.

